### Confidentiality {27}

The research data will be handled in line with the Hong Kong Hospital Authority’s policy in handling/storage/destruction of patients’ medical records.

During the trial, a de-identified database in which the student and parent names and contact numbers are eliminated will be for exchange among research team members and analyses. Only the research assistant responsible for the mobile messaging could access the password-protected file with participant identifying information. All the personal data will be destroyed after 3-years of storage.

### Plans for collection, laboratory evaluation, and storage of biological specimens for genetic or molecular analysis in this trial/future use {33}

The biological sample of selected participants will be collected and stored for oral microbiome composition analysis. Unstimulated saliva or/and dental plaque will be collected by a dentist in the study sites and stored in the investigator’s refrigerator at −80°C for future use.

## Statistical methods

### Statistical methods for primary and secondary outcomes {20a}

The effectiveness of HBM-based intervention will be evaluated by comparing the differences in the outcome variables among the three groups. For the primary outcome, linear mixed models will be constructed to compare the dental caries increment and other continuous outcome variables such as BOP% and VPI over time. Socio-demographic variables (gender and parental education level) will be controlled for. Three-level random intercept models will be considered for evaluating the clustering effect and longitudinal data: time as level 1, students as level 2, and schools as level 3 so that the interaction between times and intervention groups would be tested. Multi-level logistic regression adjusting for the effects of possible confounding factors for the clustered data [21] will be performed to test the differences in the prevalence of dental caries, and proportions of other categorical outcome variables such as frequency of toothbrushing and sugar intake among the three groups. The level of statistical significance for all tests will be set at 0.05. All the analyses will be performed using the SPSS software package.

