## Methods: participants, interventions, and outcomes

### Study setting {9}

This study will be carried out in 12 secondary schools in Hong Kong, the primary sampling unit, and formed the clusters of the trial. A list of secondary schools will be obtained from Hong Kong Education Bureau (https://www.edb.gov.hk/en/student-parents/sch-info/sch-search/schlist-bydistrict/index.html). To balance the social-economic status, 3 local co-educational public or government-subsidized schools from Hong Kong Island, 6 from Kowloon, and 3 from New Territories will be selected and randomly allocated to the 3 groups within each geographical region of Hong Kong.

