## Outcomes {12}

The primary outcome will be dental caries increment (by tooth level). The students will be examined at the schools at baseline, 1-year, and 2-year follow-up. Dental caries assessment will base on the ICDAS criteria (International Caries Detection and Assessment System), which will be used to assess both non-cavitated (codes 1 and 2) and cavitated caries lesions (codes 3–6) [16]. The examiners will examine occlusal, mesial, distal, buccal, and lingual surfaces of each tooth.

The secondary outcomes will be:i)Gingival status measured by the percentage of sites with gingival bleeding (BOP%), as recommended by the WHO for conducting oral health surveys [1];ii)Oral hygiene status using the Visible Plaque Index (VPI). The percentage of plaque on the buccal and lingual surfaces of all indicated teeth will be recorded [1];iii)Average frequency of toothbrushing per day (2 times as preferred);iv)Average frequency of intake of sugary snacks/drinks per day (2 times or less frequent as preferred);v)Average amounts of free-sugar intake per day (<25 g as preferred); andvi)Oral health self-efficacy on behaviors (questionnaire score rated on a 4-point Likert scale, e.g., 1 = not confident at all to 4 = very confident)

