## Assignment of interventions: allocation

### Sequence generation {16a}

Following the recruitment of 12 schools, schools will be randomly allocated to each of the study groups. The allocation sequence will be generated using Microsoft Excel by the project statistician not involved in the data collection.

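### The stated linear mixed models adjust for gender and parental education but not for baseline caries or the randomisation regions; this mainly costs efficiency and calibration, and omitting region does not bias the comparison

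*Protocol article*

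**What the plan says.** All references are to the protocol article.

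- **Model.** Under Statistical methods {20a}, "linear mixed models will be constructed to compare the dental caries increment and other continuous outcome variables such as BOP% and VPI over time". Three-level random-intercept models are to be considered, with "time as level 1, students as level 2, and schools as level 3 so that the interaction between times and intervention groups would be tested".
- **Covariates.** The same section states "Socio-demographic variables (gender and parental education level) will be controlled for". Neither baseline caries nor region is mentioned there. The categorical outcomes are handled differently: "Multi-level logistic regression adjusting for the effects of possible confounding factors for the clustered data", with the factors not named.
- **Randomisation.** Study setting {9} takes 3, 6 and 3 schools from the three regions, to balance socio-economic status, and has them "randomly allocated to the 3 groups within each geographical region of Hong Kong". Sequence generation {16a} says only "Following the recruitment of 12 schools, schools will be randomly allocated to each of the study groups" and does not repeat the regional restriction.
- **Baseline data.** Outcomes {12} makes caries increment the primary outcome and states "The students will be examined at the schools at baseline, 1-year, and 2-year follow-up". The baseline value is therefore available for every examined student.

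**The concern.** Two variables that the design itself makes important are missing from the stated adjustment set.

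**Baseline caries.** An increment removes the starting level from the outcome. If students with more caries at baseline also develop more new caries, an arm that happens to start worse will show a larger increment without any treatment effect. Four schools per arm give limited protection against such a chance difference. Leaving out a prognostic baseline also gives up precision in a trial with 9 between-school degrees of freedom (12 schools minus 3 arms).

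**Region.** Allocation within region removes regional differences from the between-arm contrast. If the model ignores region, those differences stay in the error term, so the standard error is larger than the design warrants. The test then rejects too rarely and power is lost.

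**Working it through.** **Inputs from Sample size {14}.** Effect size f = 0.21; means 0.12 and 0.34 with SD about 0.50, so the difference is 0.22/0.50 = 0.44 SD; two-sided 5% taken for pairwise contrasts; power 80%; ICC 0.03; 75 students per school; 10% dropout; 4 schools per arm, 12 in all. Completers per school: 75 × 0.9 = 67.5.

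**Assumed inputs.** The protocol gives no correlation r between baseline caries and increment (0.1, 0.3 and 0.5 tried) and no share of between-school variance explained by region (0 to 50% tried).

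**1. The plan's own figures.**
- Three-group ANOVA with f = 0.21 and 74 per group has power 0.801, so 74 reproduces.
- Design effect: 1 + 74 × 0.03 = 3.22, which reproduces.
- 74 × 3.22 = 238.3, and 238.3/0.9 = 265 per group. Rounded up to whole schools of 75, this gives 300.

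**2. Chance imbalance at baseline** (same ICC assumed for baseline caries; any gain from stratification ignored).
- SD of the difference between two arm means = √(2 × 3.22/300) = 0.147 SD.
- A gap above 0.25 SD between two given arms: 0.25/0.147 = 1.71, probability about 9%.
- With r = 0.3 to 0.5 such a gap shifts the unadjusted contrast by 0.25 × r = 0.075 to 0.125 SD, which is 17 to 28% of the planned 0.44 SD. With r = 0.1 the shift is 0.025 SD, or 6%.

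**3. Power at school level without either variable.**
- Variance of a school mean = 0.03 + 0.97/67.5 = 0.0444, of which 0.03/0.0444 = 68% is between schools.
- Noncentrality = 12 × 0.21²/0.0444 = 11.9. The F test on 2 and 9 df has power 0.74.

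**4. Adding baseline.** Both variance components are multiplied by 1 − r².

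| r | power, 9 df | power if baseline is charged one school-level df (8 df) |
|---|---|---|
| 0.1 | 0.745 | 0.72 |
| 0.3 | 0.78 | 0.76 |
| 0.5 | 0.86 | 0.84 |

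**5. Adding region.** The between-school component is multiplied by 1 minus the regional share, and the error df fall from 9 to 7.

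| regional share | power, 7 df |
|---|---|
| 0% | 0.69 |
| 10% | 0.73 |
| 20% | 0.76 |
| 30% | 0.79 |
| 50% | 0.86 |

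Break-even on interval width: the t critical value rises from 2.262 to 2.365, and (2.365/2.262)² = 1.093. Region must therefore remove 1 − 1/1.093 = 8.5% of the variance of a school mean. That is 0.085/0.68 = about 12.5% of between-school variance. Judged on the F-test power above, the figure is nearer 15%.

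**6. Ignoring region after stratifying on it.** In 40,000 simulated trials per setting, with 1/2/1 schools per arm by region:

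| regional share | type I error, region ignored | type I error, region fitted |
|---|---|---|
| 0% | 0.051 | 0.050 |
| 20% | 0.031 | 0.049 |
| 30% | 0.024 | 0.051 |
| 50% | 0.011 | 0.049 |

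The error is always in the conservative direction.

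**The case against.** - **Baseline is already used.** The primary outcome is an increment, and a time-by-group interaction is tested. If the baseline visit is one of the time points, a baseline difference goes into the group main effect and not into the tested term. This stands against any reading that chance imbalance is left wholly uncorrected. It does not cover a remaining association between baseline caries and new caries.
- **Region cannot bias the comparison.** Three, six and three schools allocated 1:1:1 within region give each arm 1/2/1. A reader might infer that regional imbalance distorts the result or inflates false positives. The design as described in Study setting {9} excludes the first, and the simulation shows the opposite of the second.
- **Region may not pay.** Two of nine df is a real price with 12 schools, and parental education, already in the model, may absorb part of the socio-economic difference that region stands for. This stands: the protocol gives no figure showing that regions differ in caries increment, so a gain cannot be asserted.
- **Entering baseline everywhere would be wrong.** Where the baseline visit is already a repeated response, adding it as a covariate uses one measurement twice. This stands and shapes the fix.
- **Scope.** The article condenses a fuller document, does not say that the two covariates are the only ones, and leaves the logistic models' confounders unnamed. The point is therefore confined to the linear mixed models. There, a named list is stated and lacks both variables.

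**Conclusion.** The point holds as a recommendation on efficiency and calibration. The adjustment set stated for the linear mixed models omits the measured baseline of the primary outcome and the factor used to restrict the randomisation.

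For baseline caries, the benefit runs from negligible (r = 0.1, with a small loss if a school-level df is charged) to substantial (power 0.84 to 0.86 at r = 0.5, against 0.74). For region, omission leaves the comparison unbiased. If regions differ, the test is conservative and power is lost; if they do not, fitting region lowers power from 0.74 to about 0.69.

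These figures rest on ICC 0.03 applying to both baseline and outcome, 67.5 completers per school, and assumed ranges for the correlation and the regional share. The 1/2/1 balance rests on Study setting {9}, since Sequence generation {16a} does not restate it. The documents support neither a claim that the planned analysis is biased by region nor a claim that adding region is certain to gain precision.

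**What to change.** 1. Add baseline caries as a covariate in the caries-increment model.
2. For BOP%, VPI and the questionnaire scores, choose one approach and state it: adjust for the baseline value with only follow-up visits as responses, or keep baseline as a response in the longitudinal model. Do not do both.
3. Add region (three levels) as a fixed effect, with a small-sample degrees-of-freedom correction suited to 12 schools. If region is left out, give the reason, such as the df cost.
4. Repeat the within-region allocation under Sequence generation {16a}, so that it agrees with Study setting {9}.

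The cost is a few sentences, fixed before outcomes are seen, and no new data. The statistical price is 2 of 9 between-school df for region, which is recovered only if region explains about 12.5% or more of between-school variance.

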### Trial design {8}

This study is a three-arm parallel design, superiority, cluster-randomized controlled trial comparing three interventions. Interventions will be applied at the cluster (school) level. Either active or comparator intervention is administered to the school by randomization to prevent contamination. The allocation ratio is 1:1:1.

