## Sample size {14}

The sample size has been calculated using G*Power software. Our previous study showed that motivational interviewing was more effective than prevailing OHE in preventing dental caries among adolescents [17]. In this proposed study, the sample size is calculated based on mean and standard deviations of the primary outcome measure — the number of new carious teeth (∆DMFT). From the pre-existing study, an effect size of 0.21 was obtained for tooth status over 24-month evaluation (∆DMFT: test group=0.12 vs. control group=0.34; SD ~ 0.50) [18], which could be considered a moderate size convention for 1-way ANOVA and clinically significant for the primary outcome [19]. Based on a significance level of 5% and a targeted statistical power of 80%, 74 participants in each group will be required. Considering a typical value of ICC = 0.03 in a cluster randomized clinical trial setting [20] and if 75 children are to be recruited from each school, the design effect will be 3.22 [21]. Assuming a similar dropout rate as our previous study in secondary school at the 2-year follow-up (dropout rate: 10%) [17], the sample size will be increased to 300 in each group, thus 900 altogether. Then 4 schools in each group, a total of 12 schools will be recruited.

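### The time-by-group test in a random-intercept-only model leaves school-level variation in change out of its standard error; if the plan's ICC of 0.03 applies to change, type I error is well above 5%

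*Protocol article*

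**What the plan says.** Trial design {8} makes the school the unit of allocation: "Interventions will be applied at the cluster (school) level". Sample size {14} gives four schools per arm, 12 in all.

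The same section works from the 24-month caries increment: "the sample size is calculated based on mean and standard deviations of the primary outcome measure", with "test group=0.12 vs. control group=0.34; SD ~ 0.50". It then allows for clustering: "Considering a typical value of ICC = 0.03 in a cluster randomized clinical trial setting". With 75 students per school it obtains a design effect of 3.22. So the ICC is applied to a calculation whose outcome is change, not level.

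Statistical methods for primary and secondary outcomes {20a} proposes linear mixed models for the caries increment and for BOP% and VPI over time. On structure it says: "Three-level random intercept models will be considered for evaluating the clustering effect and longitudinal data". Visits are level 1, students level 2 and schools level 3, and the stated purpose is to test the interaction of time with group. No random slope and no school-by-time term is named. On the error rate: "The level of statistical significance for all tests will be set at 0.05".

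Outcomes {12} schedules caries examinations at baseline, 1 year and 2 years.

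**The concern.** A school random intercept moves every visit of every student in that school by the same amount, and a student intercept does the same for one student. Neither affects a difference between two visits. When the response is the value at each visit and the effect is read from time-by-group, both intercepts drop out, and what remains in the error term is variation between visits within students.

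The model therefore handles schools that differ in their usual level of caries, plaque or bleeding. It does not handle schools that differ in how much their students change over two years. With four schools per arm, such differences do not average out well, and a chance difference between two sets of four schools could be declared an intervention effect. The sample size allows for school variation in the increment; the tested term does not.

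**Working it through.** **1. The plan's own figures.** A one-way ANOVA with three groups, f = 0.21, alpha 0.05 and 80% power needs 74 per group (power 0.801), as stated. Design effect: 1 + (75 − 1) × 0.03 = 3.22, as stated. Then 74 × 3.22 = 238.3; 238.3 / 0.90 = 264.8, so 265; 265 / 75 = 3.53 schools, rounded up to 4 schools × 75 = 300 per group. The sample size reproduces.

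**2. Inputs to the check.** Analysed students per school: 75 × 0.90 = 67.5, so 270 per arm and 810 in all. ICC 0.03, assumed to apply to change. Two-sided alpha 0.05 (the protocol does not state sidedness).

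**3. What the model uses as error.** For student i in school j at visit t, the model is Y = group-by-time mean + s_j + u_ij + e_ijt. The 2-year change is D = (arm mean change) + e_ij2 − e_ij0; s_j and u_ij have gone. With 810 students at three visits, the residual has 810 × 2 − 2 − 4 = 1,614 degrees of freedom, whereas 12 schools in three arms give 12 − 3 = 9.

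**4. Size of the understatement.** If D has intraschool correlation ρ, the true variance of an arm contrast is DE = 1 + (m − 1)ρ times the variance the model reports. At ρ = 0.03, DE = 1 + 66.5 × 0.03 = 2.995, so standard errors are too small by √2.995 = 1.73. With the plan's SD of 0.50 and 270 per arm, the model's standard error for a difference is 0.50 × √(2/270) = 0.043, against 0.043 × 1.73 = 0.074. The 95% half-width is 0.084 where it should be at least 0.146.

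**5. Type I error, two-visit formula.** Pairwise: 2(1 − Φ(1.96/√DE)). Three-arm, 2 df: P(χ²₂ > 5.991/DE). With m = 67.5:

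| ICC of change | DE | Pairwise | Three-arm |
|---|---|---|---|
| 0.005 | 1.333 | 9% | 11% |
| 0.01 | 1.665 | 13% | 17% |
| 0.02 | 2.330 | 20% | 28% |
| 0.03 | 2.995 | 26% | 37% |
| 0.05 | 4.325 | 35% | 50% |

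At ICC 0 the formula returns 5%.

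**6. Simulation** (12 schools, 68 students each, 4,000 runs per scenario). At ICC 0.03, two visits gave 25–27% pairwise and 36–38% for three arms. Three visits gave 27–36% and 32–51%, depending on the within-student covariance. Part of that three-visit excess is not a school effect: with no school variation in change, the pairwise test still ran at 5–11%, because random intercepts alone imply a covariance pattern that may not hold.

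**7. Increments as the response.** At ICC 0.03, a school random intercept fitted to the 2-year increment gave 5.4% for the group effect. With the 1-year and 2-year increments as two responses, the time-by-group interaction was still rejected in 11–38% of runs across covariance patterns and tests.

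**8. School-level error.** An F(2, 9) test on school mean 2-year change gave 4.8–5.1% at ICC 0.03.

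**The case against.** The strongest reply is that {20a} speaks of comparing the caries increment, which is also how {12} and {14} define the primary outcome. If the increment is the response, the school intercept does carry school variation in change, and the group main effect is tested at close to 5%. This stands, and it means one cannot say that the planned model has no term for that variance under every reading. But the test that {20a} names is the interaction. With increments as the response, it asks whether the arm difference alters between year 1 and year 2, which is not the 2-year treatment effect, and it is still inflated. For BOP% and VPI, analysed over time, values at each visit are the natural response.

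Second, the ICC is a generic figure borrowed for cluster trials, not an estimate of school variation in caries change. This also stands. If school differences were constant over time, omitting a school-by-time term would do no harm.

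Third, the model is only to be considered, the article is condensed, and an analysis plan may settle the structure. That leaves room for correction. It does not remove the point, because the article states both the random-effects structure and the test, and the combination is the difficulty.

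A reader might infer that the primary analysis will certainly have a false-positive rate of 26–37%. The documents do not support that: it requires values at each visit as the response, an ICC of 0.03 for change, and the two-visit calculation.

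**Conclusion.** The point holds in conditional form. As worded, the random-intercept model and the interaction test together leave school-level variation in change out of the standard error, while the sample size allows for exactly that variation.

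With values at each visit as the response and the plan's ICC applied to change, type I error is about 26% pairwise and 37% for three arms in the two-visit calculation, and standard errors are too small by a factor of about 1.7. Any positive ICC of change inflates the error; the school component vanishes only if schools do not differ in change. With three visits the figure also depends on the within-student covariance. With increments as the response, the group main effect is sound and only the named interaction is at fault. The article does not settle which reading applies, so the primary contrast needs to be stated before analysis.

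**What to change.** State in {20a} that the primary test is the arm effect on the 24-month caries increment, one value per student, in a two-level model (students within schools) with a school random intercept and small-sample degrees of freedom reflecting 12 schools (about 9).

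If the longitudinal model is kept, including for BOP% and VPI, add a random school-by-time effect so that time-by-group contrasts are tested against between-school variation. The choice of within-student covariance can be left to the analysts.

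The cost is a sentence or two and no new data. Confidence intervals become wider: in the illustration above, the half-width goes from 0.084 to about 2.262 × 0.0745 = 0.17 with 9 degrees of freedom, against a planning difference of 0.34 − 0.12 = 0.22. The sample size already allows for the design effect part of that widening.

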**Methods:**

This is a three-arm parallel-design cluster-randomized controlled trial. This trial will allocate 12 local secondary schools (clusters) in Hong Kong to three test or comparison groups with a ratio 1:1:1. The enrolled Form II to IV students (ages 12 to 15) will be eligible for participation. The intervention to three study groups will be (i) Health Belief Model (HBM)-based mobile messaging to the adolescents and their parents, which will consist of several blocks of HBM-based messages and reinforcement during 24 weeks; (ii) same HBM-based messaging to adolescents only; and (iii) delivering e-version of oral health education pamphlets to adolescents. The primary outcome will be caries increment 2 years post-intervention. Changes in oral health self-efficacy and behaviors, oral hygiene, and gingival status will be the secondary outcomes.

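### If increments from baseline at 1 and 2 years enter one random-intercept model with a single residual variance, the standard error of the primary 2-year contrast is too small, by an amount that the protocol's figures do not fix

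*Protocol article*

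**What the plan says.** The abstract fixes the time point: "The primary outcome will be caries increment 2 years post-intervention". Outcomes {12} sets the visits: "The students will be examined at the schools at baseline, 1-year, and 2-year follow-up". That gives each student two increments from baseline.

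Statistical methods for primary and secondary outcomes {20a} says that "linear mixed models will be constructed to compare the dental caries increment and other continuous outcome variables such as BOP% and VPI over time". On the model it says: "Three-level random intercept models will be considered for evaluating the clustering effect and longitudinal data". Visits are level 1, students level 2 and schools level 3, and the stated purpose is "so that the interaction between times and intervention groups would be tested". The section names no random slope, school-by-time effect or visit-specific variance. It does not say whether the increment is counted from baseline or from the previous visit.

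Sample size {14} gives the 24-month increment only: "DMFT: test group=0.12 vs. control group=0.34; SD ~ 0.50". No year-1 variance and no correlation between visits is given.

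**The concern.** On the natural reading, a student's increments from baseline at year 1 and year 2 are the two level-1 values. The second equals the first plus the new caries of the second year, so its variance should be larger. Random intercepts for student and school with one residual variance cannot represent this. They give both visits the same marginal variance, which ends up near the average of the smaller year-1 and the larger year-2 variance.

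The year-2 arm contrast, which is the primary comparison, would then be judged against too small an error: its interval is too narrow and its p-value too small. The year-1 interval errs the other way. Adding a school-by-time term does not cure this, because that term also has one variance for both visits.

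**Working it through.** **The plan's own figures.** Design effect: 1 + (75 − 1) × 0.03 = 3.22, as stated. 74 × 3.22 = 238.3; divided by 0.9 this is 265 per arm, rounded up to 4 schools × 75 = 300. So ICC 0.03, 12 schools and 10% dropout (75 × 0.9 = 67.5 analysed per school) can be used as inputs. The plan states no standard error to reproduce.

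**Assumption not in the protocol.** Let r = Var(year-1 increment) / Var(year-2 increment). At constant incidence with independent yearly increments, r = 0.5. The 24-month figures fit this loosely: means of 0.12 and 0.34 against a variance of 0.50² = 0.25 are near Poisson. Examination error of equal size at both visits raises r. If a share q of the year-2 variance is true caries, r = 0.5q + (1 − q), so q = 0.8 gives 0.6 and q = 0.4 gives 0.8.

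**Year-2 variance of a school mean** (SD 0.50, ICC 0.03):
- School part: 0.03 × 0.25 = 0.0075.
- Student part: 0.97 × 0.25 / 67.5 = 0.00359.
- V2 = 0.01109. With 4 schools per arm, the true standard error of an arm contrast is √(2 × 0.01109 / 4) = 0.0745.

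**The equal-variance fault alone** (school-by-time term included). The fitted variance is (V1 + V2)/2. If r is the same at both levels, the ratio of fitted to true standard error is √((1 + r)/2):

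| r | ratio | shortfall |
|---|---|---|
| 0.4 | 0.837 | 16.3% |
| 0.5 | 0.866 | 13.4% |
| 0.6 | 0.894 | 10.6% |
| 0.8 | 0.949 | 5.1% |

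For year 1 at r = 0.5 the ratio is √(0.75/0.5) = 1.22, so that standard error is about 22% too large.

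**Random intercepts only** (no school-by-time term), r = 0.5, independent yearly increments at both levels. The fitted variance of a school mean at one visit is the variance of the two-visit school average plus the residual variance divided by 2m.
- School part of the average: 0.00375 + 0.00375/4 = 0.00469.
- Student part: (0.12125 + 0.12125/4)/67.5 = 0.00225.
- Residual variance: Var(y2 − y1)/2 = 0.125/2 = 0.0625; divided by 2 × 67.5 this is 0.00046.
- Sum 0.00740; √(0.00740/0.01109) = 0.816, a shortfall of 18.4%.

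At r = 0.4 the shortfall is about 22%. The part beyond the table above belongs to the missing school-by-time term.

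**School effect constant from year 1**, student r = 0.5. V1 = 0.0075 + 0.00180 = 0.00930; √((0.00930 + 0.01109)/(2 × 0.01109)) = 0.959, a shortfall of 4.1%.

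**Simulated null trials** (6000 per setting, 12 schools, 68 students each, t reference on 9 degrees of freedom, r from 0.4 to 0.6, school effects accumulating):
- Equal-variance fault alone: standard error 0.84-0.90 of true, type I error about 7-9%.
- 2-year increment analysed alone: type I error 4.7-5.4%.

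**The named interaction.** With two increments per student it is the arm difference in y2 − y1. Unequal marginal variances do not distort the variance of that difference. In 4000 null trials per setting with a school-by-time term, its type I error was 4.4-5.3%. It is a different quantity, however. If the sample-size difference of 0.34 − 0.12 = 0.22 built up evenly, the year-1 difference would be 0.11 and the interaction 0.22 − 0.11 = 0.11.

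**The case against.** Four points can be made on the other side.

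1. The only test that {20a} names is the interaction, and this fault leaves it intact. That stands. But the abstract makes the 2-year increment primary, and {20a} also says that the model will compare the increment, so a year-2 contrast has to come from somewhere. If it is read from this model, the fault applies.
2. The models are only to be considered, no residual structure is named, and an analysis plan that is not shown may allow visit-specific variances. This also stands, so the point is conditional. It is not a complaint about missing detail. It says that the one structure named for repeated visits, used in its usual form, does not suit a cumulative increment.
3. The response may not be cumulative. With per-interval increments the nesting argument fails, but then neither visit's value is the 2-year increment. If caries status at 0, 1 and 2 years were modelled instead, the year-2 interaction term would estimate the 2-year change, and its standard error under random intercepts would be about 18-29% too small at student level.
4. The size is assumed. A reader might infer that the standard error is 10-22% too small as a fact. The documents do not support that: they give no year-1 variance, and the 22% end includes the separate school-by-time omission.

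**Conclusion.** The point holds as a conditional one. If increments from baseline at both visits are modelled with random intercepts and one residual variance, the year-2 arm contrast has too small a standard error. The direction follows whenever the year-2 variance is the larger.

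The size rests on assumptions. With a year-1 variance of 0.4 to 0.6 of the year-2 variance and school effects that also accumulate, the shortfall from this fault alone is about 10-16%, with type I error of about 7-9% instead of 5%. Without a school-by-time term it reaches about 22%. If the ratio is near 0.8 or the school effect is constant from year 1, it is about 3-7%, which is minor.

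It would be wrong to conclude that the planned interaction test is invalid for this reason. Its weakness here is that, on increments at 1 and 2 years, it does not estimate the 2-year difference that the trial calls primary. The change is worth making because the primary comparison is exposed and the remedy is small.

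**What to change.** State in {20a} that the primary estimate comes from a linear mixed model of the 2-year increment alone, with a school random intercept and school-level degrees of freedom (12 schools − 3 arms = 9).

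Alternatively, keep both visits but give year 1 and year 2 their own variances and a covariance at student level and at school level, and report the year-2 arm contrasts as primary. In either case, say that the increment is counted from baseline.

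The cost is a sentence or two and, for the second option, a different covariance specification. No further data are needed. The 2-year interval becomes slightly wider: at r = 0.5 the standard error goes from 0.866 × 0.0745 = 0.0645, the value with a school-by-time term, to 0.0745.
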